## Abstract

**Background:**

Physical activity (PA) is a key behaviour for patients with type 2 diabetes (T2DM). However, healthcare professionals’ (HCP) recommendations (walking advice), which are short-term and individually focused, did not reduce the PA drop-out ratio in the long run. Using a socio-ecological model approach may contribute to reducing patient dropout and improving adherence to PA. The aim of this study is threefold: first, to evaluate the effectiveness of a theory-driven Nordic walking intervention using a socio-ecological approach with T2DM patients in Spain; second, to explore the feasibility on the PA adherence process in T2DM patients while participating in the SENWI programme; and third, to understand the HCPs’ opinion regarding its applicability within the Spanish healthcare system.

**Methods:**

A three-arm randomized control trial (*n* = 48 each group) will assess the efficacy of two primary care-based PA interventions (Nordic walking vs. Nordic walking plus socio-ecological approach; two sessions per week for twelve weeks) compared to a control group (usual HCPs’ walking advice on PA). Inclusion criteria will include physically inactive patients with T2DM, older than 40 years and without health contraindications to do PA. PA levels and drop-out ratio, quality of life and metabolic and health outcomes will be assessed at baseline, post-intervention and at 9- and 21-month follow-ups. The effect of the different interventions will be assessed by a two-factor analysis of variance: treatment group vs time. Also, a two-factor ANOVA test will be performed with linear mixed models for repeated measures.

A qualitative analysis using focus groups will explore the reasons for the (in)effectiveness of the new PA interventions. Qualitative outcomes will be assessed at post-intervention using thematic analysis.

**Discussion:**

Compared with the general PA walking advice and Nordic walking prescriptions, integrating a socio-ecological approach into Spanish primary care visits could be an effective way to reduce the PA drop-out ratio and increase PA levels in patients with T2DM. Such interventions are necessary to understand the role that multiple socio-complex process in day-to-day PA behaviour has in patients with T2DM in the Spanish context.

**Trial registration:**

ClinicalTrials.gov NCT05159089. Physical Activity Drop-out Ratio in Patients’ Living with Type 2 Diabetes. Prospectively registered on 15 December 2021.

**Supplementary Information:**

The online version contains supplementary material available at 10.1186/s13063-022-06742-7.

**Table Tabb:** 

**Data category**	**Information**
Primary registry and trial identifying number	ClinicalTrials.gov NCT05159089
Date of registration in primary registry	15 December 2021
Secondary identifying numbers	-
Source(s) of monetary or material support	Col·legi de Fisioterapeutes de Catalunya
Primary sponsor	Col·legi de Fisioterapeutes de Catalunya
Secondary sponsor(s)	n/a
Contact for public queries	[name] ([contact])
Contact for scientific queries	[name] ([contact])
Public title	
Scientific title	
Countries of recruitment	Spain
Health condition(s) or problem(s) studied	Type 2 diabetes mellitus, physical activity adherence
Interventions	Active comparator: Nordic Walking plus the socio-ecological model
	Active comparator: Nordic Walking intervention
	Control comparator: general nurses healthcare follow-up
Key inclusion and exclusion criteria	Ages eligible for study: ≥45 years Sexes eligible for study: both Accepts healthy volunteers: no
	Inclusion criteria: patients with type 2 diabetes
	Exclusion criteria: with contraindications to do physical activity
Study type	Interventional
	Allocation: randomized intervention model. Parallel assignment masking: single blind (evaluator)
	Primary purpose: treatment
	Phase I
Date of first enrolment	14-02-2022
Target sample size	144
Recruitment status	Recruiting
Primary outcome(s)	Physical activity drop-out ratio, physical activity levels, metabolic and health outcomes (HbA1c, blood pressure, waist circumference and BMI) and quality of life.
Key secondary outcomes	Socioeconomic status, social network index and demographic information (sex, gender, age, ethnic origin, marital and family status and medication)

## Background

Physical activity (PA)—understood as any body movement that requires energy expenditure above the resting metabolic rate—is a key behaviour for people living with type 2 diabetes mellitus (T2DM) [1, 2]. In these patients, increasing daily PA has a dose-response relationship with markers of glucose control (i.e., HbA1c) [3]. Moreover, being physically active also produces psychological and social benefits: it improves patients’ quality of life and reduces the healthcare costs associated with physical inactivity [4–6].

PA recommendations in patients with T2DM include at least 150–300 min of moderate-to-vigorous intensity (MVPA) most days of the week with a multicomponent training including aerobic and muscle-strengthening activities [7]. In addition, the amount of time spent being sedentary should be limited [8]. In this regard, adhering to regular PA—understood as not dropping out of the newly adopted PA behaviour [9]—is a way to control T2DM and promote self-management [10–12]. To achieve these goals, the preferred modality of health care professionals (HCP) to encourage and increase PA is walking. Walking 30 min a day is a popular recommendation for increasing PA and reducing time spent being sedentary that HCPs are able to make in health care consultations with these patients [13]. However, after decades of primary care-based PA recommendations and interventions, patients report dropout rates of 20–50% within the first 3–6 months of intervention [14, 15], and in the long run (e.g. 12–24 months), the interventions seem ineffective [16, 17].

To deal with this dropout problem, high-intensity interval training, which requires less time to achieve the same benefits as moderate intensity [18], has been proposed as a possible solution to overcome one of the most frequently reported barriers to adherence (namely, lack of time) [19, 20]. However, the advanced skills required and the necessary good physical condition to withstand these kind of protocols [21, 22] may not be a suitable solution for most patients [23]. Another option to reduce patients’ PA drop out is Nordic walking (NW) [24]. NW provides more health benefits (e.g. glucose control, cardio-respiratory fitness, flexibility and upper-body strength) than merely walking [25, 26], and it is easier to perform than high-intensity interval training [27]. However, although NW seems to be more enjoyable than simply walking, the PA drop-out ratio remains high [24].

Current interventions such as NW mainly focus on adopting PA recommendations without facing the main issue in public health: treatment adherence [28]. Gender, social support, built environment and sociodemographic context have been identified as relevant determinants for being physically active [29–31]. Studies reporting dropout from long-term PA programmes show that people with low education and socioeconomic status have a higher prevalence than their counterparts [14]. Moreover, a previous qualitative study identified that not only social inequity [32, 33] but also having non-negotiable kinship needs (e.g. family care) may effect treatment adherence [34].

In this context, HCPs’ poor results in making PA part of patients’ routine (i.e. adherence) may be due to the complexity of patients’ daily social life (e.g. structural barriers) where HCPs do not have any influence [9, 34, 35]. Structural barriers (e.g. political decision-making) may have more influence on PA routinization than patients’ motivation and knowledge [34, 36]. Yet, ineffective primary care-based PA recommendations may enhance socioeconomic barriers and health inequity in T2DM patients [32, 33].

PA adherence is a complex public health issue with multiple interacting influences. Thus, focusing on a single solution to improve PA adherence may be more helpful in achieving short-term and individual-level health outcomes than multiple long-term and population-level outcomes [37].

Using a socio-ecological model (SEM) approach in primary care-based PA practices may help to reduce patient drop-out rate and improve adherence to PA [38, 39]. SEM considers the complex interplay between individual, relationships, community and societal factors that influence both the adoption and the adherence of the treatment [40]. Thus, this approach focuses on changing the physical and social environments as well as modifying individual health-related factors [41]. This may involve facing different sociocultural barriers, including socioeconomic status and social inequity (e.g. delivering free guided intervention), gender- and age-specific needs (e.g. providing tailored information with a professional support), or built environment (e.g. enrolling neighbourhood green open spaces). However, HCPs might find it difficult to address such sociocultural and environmental barriers in short visits [11, 42]. Given the scale and span of the PA biological, psychological and social benefits for patients with T2DM, it is a public health priority to deploy more effective ways to implement day-to-day PA prescriptions in primary care practices.

This study protocol has two aims. The primary aim is to evaluate the effectiveness of a theory-driven Nordic Walking intervention—based on SEM (SENWI)—in people with T2DM that will be implemented in real-life primary care clinical practice in Spain. Second, we wish to explore the feasibility of the PA adherence process in T2DM patients while participating in the SENWI programme and to understand the HCPs’ opinion regarding its applicability within the Spanish healthcare system.

## Methods/design

### Study design

A mixed methodology will be used. First, a three-arm randomized control trial will compare the effectiveness of a 12-week SENWI programme, a NW programme and typical healthcare advice on PA. The main outcomes will be assessed at baseline, post-intervention and at 9- and 21-month follow-ups. Second, a qualitative thematic analysis using focus groups will aim to understand patient and HCP experiences of the SENWI intervention and factors that may enable or limit patients’ PA drop-out ratio, both of which will be assessed at post-intervention (T1). The study protocol (NCT05159089) was developed based on the Standard Protocol Items: Recommendation for Interventional Trials (SPIRIT) guidelines [43].

An intern Audit Committee will be made up of two research members ([name] and [name]): a specialist in PA research and a statistician. This committee will verify the processes related to recruitment, informed consent, eligibility, assignment to the treatment groups and adherence to the intervention every month. The Committee will meet monthly and will support day-to-day organization of all research teams.

### Participants

A total of 144 participants (randomized in two intervention groups and one control group) will be included in this study. The study will be conducted in the Central Catalonia health area (Spain). Participants will be recruited from Monistrol de Montserrat *Primary Care Center* (CAP), Vic Sud CAP (Vic), CAP les Bases (Manresa), Hospital *Sant Bernabé* (Berga) and Anoia CAP (Igualada).

Inclusion criteria for eligibility will include participants (i) with T2DM, (ii) that have no major physical limitations prescribed by the doctor or any HCP and (iii) that are physically inactive according to the Spanish version of a Brief Physical Activity Assessment Tool – SBPAAT screening tool [44]. Participants will be excluded if they (i) are pregnant or have T2DM due to gestation; (ii) are unable to freely consent to take part in the study; (iii) are unable to understand the study materials or PA intervention; (iv) have complications such as neuropathy, retinopathy and nephropathy; (v) have relative or absolute contraindications to do PA; and (vi) have a body mass index over 34.9 kg/m^2^ since Nordic walking uses poles that require free arm mobility that is impaired by a body mass index over 35 kg/m^2^.

### Sample size

We calculated the sample size (*n* = 144) in relation to the drop-out ratio in PA interventions showed by other studies (15%) [45] with a balanced one-way analysis of variance power calculation of 80%, a significance level of 5%, an expected drop-out rate in participants of 15% and an effect size of 0.5. As a result, 48 participants will be needed in each group in the three-arm randomized controlled trial.

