**Table 3 Tab3:**
[figure not shown]
Study timeline

Primary outcomes include (i) PA drop-out ratio; (ii) PA levels; (iii) metabolic and health outcomes (HbA1c, blood pressure, waist circumference and BMI); and (iv) quality of life (SF-12) (see Table 4).

**Table 4 Tab4:** Overview of outcomes, outcome measures, instruments and assessment time points

Outcomes	Outcome measures	Instrument/who measures	Assessment time point
Personal information	Age, gender, civil status, living arrangement, educational background, medical conditions, smoking and alcohol habits.	Primary care records/self-report	T0
Primary clinical trial outcomes			
●Physical activity	Daily counts per minute and intensity of exercise, and daily step counts.	ActivPal®/research team	T0, T1, T2, T3
●Physical activity drop-out ratio	Less of 80% of attendance during the intervention or auto-reported drop out after intervention (yes/no)	Excel/research team	T0, T1, T2, T3
●Quality of life	Physical function, physic role, corporal pain, general health, vitality, social function, emotional role and mental health	SF-12 questionnaire/research team	T0, T1, T2, T3
●Blood pressure	Systolic and diastolic blood pressure; heart rate	OMRON M6 comfort/nurse	T0, T1, T2, T3
●Blood glucose levels (last 3 months)	HbA1c	CATSALUT Dataset	T0, T1, T2, T3
●Anthropometry	Waist circumference and BMI	Measuring tape and coefficient between weight and height/nurse	T0, T1, T2, T3
Secondary clinical trial outcomes			
●Socioeconomic status	Job, education and income	Job and education level and individual and family annual income/research team	T0
●Social network index	Number of social interactions with family friends or mates	Berkman et al. [47] questionnaire with adaptations [48]/research team	T0
●Demographic and background information	Sex, gender, age, ethnic origin, marital and family status or obligations and medication	Self-report information/nurse	T0, T1, T2, T3 (only apply times for medication)
Primary qualitative study outcomes			
●HCP and T2DM perspective on the intervention	Perceptions and experience to examine the feasibility about the intervention and applicability to everyday life	Focus groups /research team	T1

Assessment time points: T0 = baseline pre-intervention, T1 = at month three of intervention, T2 = at month 12 (9 months after the end of the intervention), T3 = at month 24 (21 months after the end of the intervention). *HCP*, health care professionals; *T2DM*, type 2 diabetes mellitus

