### Data analysis

Descriptive statistics will be reported as the mean and standard deviation (SD) for quantitative variables (PA and metabolic and health assessment outcomes) and using frequency rates and percentages for qualitative variables (drop-out ratio, medication, quality of life, socioeconomic status and social network). The Shapiro–Wilk test will be used to assess the normality of quantitative variables. For each outcome variable considered, the effect of the three different interventions will be assessed by a two-factor analysis of variance: the first factor will be the treatment group and the second factor will be time. To determine whether one treatment improves the scores of the study variables compared with the other, two-factor ANOVA tests will be performed with linear mixed models for repeated measures. An odds ratio and hazard ratio will be performed comparing drop outs in SENWI, NW and the control group at 3, 9 and 21 months.

Socioeconomic status and social network index will be analysed and compared in relation to the PA attendance at 3, 9 and 21 months post-intervention using the non-parametric chi-square test (*χ*^2^) and logistic regression when appropriate.

Demographic and other patient characteristics recorded (e.g. age, gender, marital status, income, education and employment) will be tabulated and analysed as covariables alongside the PA levels and PA drop-out ratio at the beginning and at 21 months post-intervention. Correlations and differences between groups and these variables will be analysed. Difference in baseline levels of outcome variables (PA, drop out, HbA1c and so forth) will be identified, and the correlation with the different covariables will be assessed.

A *p*-value of < 0.05 will be considered statistically significant. When multiple comparisons are carried out, the Bonferroni correction will be applied. All analyses will be carried out with the obtained data without employing missing data replacement techniques. Analysis will follow intention-to-treat principles. Assumptions will be tested regarding missing data, randomization and contamination. All analyses will be carried out using the R version 3.6.1 software.

The individual intervention will be regarded as successful if (i) it leads to an average increase in activity and (ii) the participant did not drop out of the PA (NW or any kind of PA) in the long run (i.e. if the patients answer yes when asked if they still do PA of some kind).

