## Conclusions

Compared with the general PA walking advice and Nordic walking prescriptions, integrating a SEM approach into Spanish primary care visits could be an effective way to reduce the PA drop-out ratio and increase PA levels in patients with T2DM. Such interventions are necessary to understand the role that multiple socio-complex process in day-to-day PA behaviour plays in patients with T2DM in the Spanish context.

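### The 80% power comes from a one-way ANOVA and is not established for PA drop-out, a yes/no primary outcome; for moderate reductions in drop-out, power is well below 80%

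*Protocol article*

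**What the plan says.** The Sample size section of the protocol article says that n = 144 was calculated "in relation to the drop-out ratio in PA interventions showed by other studies (15"%), "with a balanced one-way analysis of variance power calculation of 80%, a significance level of 5"%, together with "an expected drop-out rate in participants of 15% and an effect size of 0.5". The result is 48 per group in three groups. The section does not say whether 0.5 is Cohen's f, d, h, w or something else. It gives no second drop-out rate, odds ratio, hazard ratio or event count.

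Under Quantitative and qualitative outcomes, the list begins "Primary outcomes include (i) PA drop-out ratio; (ii) PA levels" and goes on to metabolic and health outcomes and quality of life. Table 4 records drop-out as yes/no.

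The Data analysis section assigns a two-factor ANOVA with mixed models to each outcome, and then gives drop-out its own analysis: "An odds ratio and hazard ratio will be performed comparing drop outs in SENWI, NW and the control group at 3, 9 and 21 months". On error control it says "A *p*-value of < 0.05 will be considered statistically significant" and "When multiple comparisons are carried out, the Bonferroni correction will be applied".

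The Conclusions say that the approach "could be an effective way to reduce the PA drop-out ratio and increase PA levels".

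**The concern.** A one-way ANOVA calculation describes a comparison of means of a continuous variable at one time. A standardised effect size on that scale does not fix any pair of drop-out proportions, so it gives no power for an odds ratio or a hazard ratio. Because the Sample size section names drop-out and no other outcome, a reader will attach the 80% to the claim that the socio-ecological programme (SENWI) reduces drop-out.

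The risk lies in interpretation. If SENWI truly brought a worthwhile but moderate reduction, the odds ratio could easily be non-significant. A reader who trusts the 80% could then take that as evidence that the programme does not help adherence, which is the problem the trial was set up to address.

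**Working it through.** **Inputs.** From Sample size: 3 groups, 48 per group, alpha 0.05, power 80%, effect size 0.5, attrition 15%. Evaluable per arm after attrition: 48 × 0.85 = 40.8, taken as 41. Starting drop-out rates: 15% (Sample size), 20–50% within 3–6 months (Background), more than 40% in the long run (Discussion). The documents give no target rate. Halving is an assumption made here to represent a moderate effect.

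**1. The plan's own figure.** One-way ANOVA with k = 3: noncentral F with 2 and 3(n − 1) degrees of freedom and noncentrality λ = 3·n·f².

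- f = 0.5: n = 13 gives 76.9%. n = 14 (λ = 3 × 14 × 0.25 = 10.5) gives 80.3%. So 14 per group are needed, and 14/0.85 = 16.5, i.e. 17, after attrition. At 41 per group the power is 99.9%.
- f = 0.25 (d = 0.5 halved): n = 53 (λ = 9.94) gives 80.5%, and 53/0.85 = 62.4, i.e. 63, after attrition. Power is 76% at 48 (λ = 9.0) and 69% at 41 (λ = 7.69).
- 80% at 41 per group corresponds to f of about 0.28, and at 48 to f of about 0.26.

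Neither reading gives 48.

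**2. Drop-out as a binary outcome, two arms.** Power is the sum, over all pairs of event counts (x, y), of Bin(x; n, p₁) × Bin(y; n, p₂), counting the pairs for which |x/n − y/n| / √[2p̄(1 − p̄)/n] exceeds the critical value, where p̄ = (x + y)/2n. The critical value is 1.96 for two-sided 0.05. With Bonferroni for three pairwise contrasts, the level is 0.05/3 = 0.0167.

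| Drop-out rates | Uncorrected, n = 41 / 48 | Bonferroni, n = 41 / 48 |
|---|---|---|
| 15% vs 7.5% | 20% / 23% | 8% / 10% |
| 20% vs 10% | 25% / 29% | 12% / 15% |
| 40% vs 20% | 51% / 59% | 34% / 41% |
| 50% vs 25% | 67% / 73% | 49% / 56% |
| 40% vs 13% | 82% / 87% | 67% / 76% |
| 50% vs 20% | 83% / 88% | 69% / 77% |

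Hand check for 40% vs 20% at n = 48 by the normal approximation: (0.20·√48 − 1.96·√(2 × 0.3 × 0.7)) / √(0.24 + 0.16) = (1.386 − 1.270)/0.632 = 0.18, and Φ(0.18) = 57%, close to the exact 59%.

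With 41 per arm, 80% uncorrected power needs a fall from 40% to about 13% or from 50% to about 21%. With 48 per arm, 40% vs 15% only just reaches it (80.4%). From 15% or 20%, drop-out would have to almost vanish (about 0.5% and 2% at 41 per arm).

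**3. Carrying the 0.5 over to drop-out.** The answer depends on the metric. Power at 41 / 48 per arm is 62% / 69% if 0.5 is Cohen's h. If 0.5 is an odds ratio, power is 16–38% across base rates of 15–50% and both arm sizes. If it is w in a three-group chi-square test, power exceeds 99%, but that corresponds to arm rates such as 2%, 30% and 58%.

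**4. Hazard ratio.** Events for a hazard ratio of 0.5 with equal arms: 4(1.96 + 0.842)²/(ln 0.5)² = 31.4/0.480 = 65.3, i.e. 66. A pairwise comparison has 96 participants, so 66/96 = 69% would have to drop out. With 30 or 40 events, power is 48% or 59%.

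**The case against.** The strongest reply is that the Sample size section may not be sizing drop-out at all. It gives 15% twice, and the first mention can be read as the source of the attrition allowance. The ANOVA would then be meant for the continuous primary outcomes (PA levels, HbA1c, blood pressure, waist circumference, BMI, SF-12), and the Data analysis section does assign a two-factor ANOVA to each outcome. No primary outcome is ranked above the others. This reading is possible, but the section names none of those outcomes, and drop-out has its own odds-ratio and hazard-ratio analysis. On either reading the 80% does not describe drop-out, and the text should say so.

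A reader might go further and infer that the stated 80% is false for drop-out, or that the trial cannot detect an effect on it. The documents do not support that. They state no drop-out contrast, so there is no drop-out power to refute, and their background rates do not exclude gaps large enough to give more than 80% uncorrected power, such as 50% vs 20%.

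It is also fair to question 41 per arm as the main case. In the two walking arms, low attendance during the programme is itself a drop-out event, so a participant who stops attending is not missing. The control arm has no scheduled sessions, so the argument does not extend to it, but 48 is defensible and both sizes are shown.

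**Conclusion.** The mismatch stands in this form: the 80% power is not established for PA drop-out, and for moderate reductions it is well below 80%. No halving from any starting rate in the documents reaches 80%. The range is 20–23% power from a rate of 15% up to 67–73% from a rate of 50%. From 40–50%, gaps of about 27–30 points reach 80% at both arm sizes without correction. With Bonferroni for three contrasts, 50% vs 20% has 69–77%.

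These figures assume pairwise two-sided tests at one time point, 41 to 48 evaluable per arm, and effects chosen here because the plan gives none. Separately, the 48 per group does not follow from the ANOVA inputs under f = 0.5 or f = 0.25, so reassigning the 80% to a continuous outcome would leave an unsupported figure in place.

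**What to change.** In the Sample size section:

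1. Name the outcome and the effect-size metric that the ANOVA calculation concerns, and restate the power that 48 per group gives on that metric.
2. State that this power does not apply to PA drop-out.
3. For drop-out, give the power or the detectable difference at 48 per arm, with 41 as a sensitivity case, for drop-out rates that the authors choose and justify. Use the Bonferroni-adjusted level where that rule applies.

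In the Data analysis section, state that the drop-out odds and hazard ratios will be interpreted from their confidence intervals, and that a non-significant result will not be read as no effect on drop-out.

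The cost is a change of wording and a short recalculation. Recruitment, sample size and data collection stay as they are. The downside is a less favourable stated power for drop-out.

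### The stated sample-size inputs do not give 48 per arm, so the 80% power is unsupported; the direction of the error cannot be settled because the effect-size index is not named

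*Protocol article*

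**What the plan says.** The Sample size section gives every numerical input and the result. The method is a "balanced one-way analysis of variance power calculation of 80" per cent, with "a significance level of 5%, an expected drop-out rate in participants of 15% and an effect size of 0.5". From this it concludes that "48 participants will be needed in each group in the three-arm randomized controlled trial", which makes the 144 that the Participants section repeats. Neither section says which index the 0.5 refers to, which outcome it concerns, or at which visit. No other section gives group means, a standard deviation or a correlation from which 48 could be rebuilt.

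Under Quantitative and qualitative outcomes the list opens with "Primary outcomes include (i) PA drop-out ratio". Table 4 records this outcome as yes or no, and the Data analysis section compares it by odds and hazard ratios. The continuous outcomes go into linear mixed models for repeated measures.

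**The concern.** For a one-way ANOVA the four inputs (number of groups, alpha, power, effect size) fix the sample size, and the loss allowance then fixes the number randomised. A reader can therefore check 48 directly, and the check fails. What is at stake is how the result will be read. Someone who sees a null finding will assume that it came from a trial with 80% power for an effect of 0.5, and the printed figures do not support that. The calculation also concerns means, so it says nothing about the yes/no drop-out that heads the list of primary outcomes.

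**Working it through.** **Inputs (Sample size section).** k = 3 equal arms, alpha 0.05, power 0.80, effect size 0.5, loss 15%, result 48 per arm.

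**Method.** Power = P(F′ > F_crit), where F′ is noncentral F with 2 and 3n − 3 degrees of freedom and noncentrality λ = 3·n·f². Here f = √[Σ(μᵢ − μ̄)²/3]/σ. Number randomised = n/(1 − 0.15), rounded up.

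**Turning 0.5 into f, with σ = 1**
- Cohen's f itself: f = 0.5.
- Largest difference 0.5, one arm apart (means 0, 0, 0.5): Σ = 1/6, f = √(1/18) = 0.236.
- Largest difference 0.5, third arm midway (−0.25, 0, 0.25): Σ = 0.125, f = 0.204.
- Steps of 0.5 between adjacent arms (−0.5, 0, 0.5): Σ = 0.5, f = 0.408.

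**Attempt to reproduce 48.** For f = 0.5, n = 14 gives λ = 3 × 14 × 0.25 = 10.5 on 2 and 39 degrees of freedom, critical value 3.24, power 80.3%. With n = 13 the power is 76.9%. So 14 are needed, and 14/0.85 = 16.5, or 17 randomised. The other readings go the same way. Evaluable after loss: 48 × 0.85 = 40.8, about 41.

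| Reading of 0.5 | f | n evaluable | n randomised | Power at 41 | Power at 48 |
|---|---|---|---|---|---|
| Cohen's f | 0.500 | 14 | 17 | 99.9% | 99.99% |
| Steps of 0.5 | 0.408 | 21 | 25 | 98.5% | 99.5% |
| Largest difference, one arm apart | 0.236 | 59 | 70 | 63% | 71% |
| Largest difference, third arm midway | 0.204 | 79 | 93 | 50% | 57% |

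Other readings also miss:
- f² = 0.5 gives 8 (10 randomised) and η² = 0.5 gives 5 (6 randomised).
- A between-group variance of 0.5 with unit within-group variance gives 11 (13 randomised).
- The conventional medium f = 0.25 gives 53 (63 randomised).
- A two-sided two-sample t-test at d = 0.5 gives 64 (76 randomised).
- Inflating by 1.15 instead of dividing by 0.85 does not reach 48 for any of these.

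**What 41 evaluable per arm can detect with 80% power**
- ANOVA at 5%: f = 0.283. As a largest difference this is 0.283 × 3/√2 = 0.60 with one arm apart, or 0.283 × √6 = 0.69 with the third arm midway.
- One pairwise two-sided t-test at 5%: d = 0.63. Normal approximation: (1.96 + 0.84) × √(2/41) = 0.62.
- The same at 5%/3, assuming three corrected contrasts: d = 0.73.

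**Yes/no drop-out (illustration; control rates assumed).** Power = Φ{[|p₁ − p₂|√n − 1.96√(2p̄(1 − p̄))]/√[p₁(1 − p₁) + p₂(1 − p₂)]}. Solving for 80% power at two-sided 5%:

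| Assumed control rate | Detectable rate, n = 41 | Detectable rate, n = 48 |
|---|---|---|
| 20% | about 1% | about 2% |
| 40% | about 13% | about 15% |
| 50% | about 21% | about 23% |

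The 20% and 50% are the ends of the range that the Background section cites for the first 3 to 6 months. The 40% is the long-run non-adherence figure in the Discussion. None of them is the trial's own drop-out definition, and the normal approximation is rough for rates near zero. Both columns are shown because participants who stop attending may count as events rather than as missing.

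**The case against.** The strongest reply is that the text names a one-way ANOVA, whose usual index is Cohen's f. On that reading 41 evaluable per arm give 99.9% power and the trial is larger than its inputs require, so nobody is misled to the trial's disadvantage. This stands as far as direction goes. It does not rescue 48, because 17 would have been enough.

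A second reply is that an article condenses the full protocol, where the index, outcome and visit may be named. That also stands: their absence alone would be no finding. What remains is that the figures that are printed disagree with one another.

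A third is that 48 has a plausible origin. A one-sided normal approximation at d = 0.5 without loss gives 50 per arm. A two-arm total of 126 times 1.15 gives 145. An analysis of covariance with an assumed baseline correlation of 0.5 and no loss gives 64 × (1 − 0.25) = 48. Each needs a different test, and each drops the loss allowance, brings in a correlation that is not stated, or spreads a two-arm total over three arms. None is the calculation described.

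A reader might infer two further errors, and the article supports neither:
- **Bonferroni.** The Data analysis section says "When multiple comparisons are carried out, the Bonferroni correction will be applied". Sizing the omnibus test at 5% and correcting the follow-up contrasts is ordinary practice, so this does not contradict the sizing. The divisor of 3 used above is an assumption.
- **The two mentions of 15%.** These can be read as one attrition assumption, first sourced and then restated. The wording is ambiguous but not shown to be wrong.

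**Conclusion.** The point holds as a mismatch in a stated figure. A balanced one-way ANOVA with the printed inputs and 15% loss gives 17, 25, 70 or 93 randomised per arm, depending on what 0.5 means, and does not give 48 on any reading tried. The 80% power is therefore unsupported.

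It would be tempting to conclude that the trial is underpowered. The article does not support that. Power with 41 evaluable per arm runs from 50% (largest difference 0.5, third arm midway) to 99.9% (f = 0.5), and the unnamed index decides where in that range the trial lies. The pairwise t-test figures describe a single-visit comparison without baseline data, not the planned mixed model, whose power depends on correlations that are not given. The drop-out figures rest on assumed control rates.

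The ANOVA results assume equal arms, a common standard deviation and exactly 15% loss. Even with no loss, power is 57% to 71% for a largest difference of 0.5 and above 99% for f = 0.5 or steps of 0.5, so the conclusion does not hinge on the loss figure.

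**What to change.** Keep 144 participants. In the Sample size section, name the effect-size index and the outcome and time point it refers to, and replace the power statement with one that the design delivers, for example:

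> With 48 randomised and about 41 evaluable per arm, a one-way ANOVA at 5% has 80% power for Cohen's f = 0.28. A single pairwise contrast has 80% power for d = 0.63 at an unadjusted 5%, or d = 0.73 at 5%/3 if three contrasts are Bonferroni-corrected.

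Add a sentence on why an effect of that size is worth detecting; if the trial team cannot defend it, n has to be reconsidered rather than the wording. For the yes/no drop-out outcome, give the detectable difference over a range of control rates labelled as assumptions, and say whether participants lost to follow-up count as events or as missing.

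The cost is a change of wording in the protocol and, where one exists, the analysis plan. It adds no participants, visits or procedures.
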